
### Employers

At T0, the questionnaire contains questions about the characteristics and occupation of the employer (e.g., age, gender, educational level, sector, and size of the organization (i.e., number of employees)). At the level of the employer, the secondary outcome measures that will be assessed are as follows:Self-efficacy: self-efficacy refers to the perceived ability of the employer to effectively support employees during sick leave and RTW. This measure is assessed with three items regarding meaningfulness, impact, and skills from the competence scale of the Empowerment Questionnaire [38]. Statements are measured on a 6-point Likert scale. The mean score of the sum is calculated, with higher scores indicating higher self-efficacy [38].Satisfaction with the resumption of work of the respective employee: this is measured with one self-developed question: “How satisfied are you with the work resumption process of your employee since the sick leave/over the past month/3 months?” on a 5-point Likert scale. The category represents the overall score, with a higher score indicating higher satisfaction.

## Process evaluation

In addition to the effect outcomes, the following process outcomes will be assessed at the level of the employee/employer, according to the model by Linnan and Steckler [13]:Recruitment: recruitment is measured by assessing the amount and reasons for non-participation of dyads and the usefulness of recruitment strategies used by the researchers. This is measured in CASTOR, or on paper via a return envelope, with an open-ended question, filled in by recruited employees who do not wish to participate prior to the trial. Also, a logbook related to recruitment strategies is maintained by the researchers, containing details about what recruitment strategy is used during the trial and the corresponding outcome.Use of the SME tool: the use of the SME tool is measured with self-developed questions regarding number of visits, duration of visits, tool availability, and web analytics (T2–T3). Employers are issued personalized links to enhance the tracking of web analytics using Piwik PRO. From this information, we can derive the administered and received dose [17, 39].Perceived usefulness of the SME tool: the perceived usefulness of the SME tool is measured with self-developed questions regarding the usefulness of the tool, enhancement of knowledge and skills, and likelihood of recommending the tool to colleagues (T3) [17].Components of the logic model of change: according to our logic model of change (see Additional file 1), we expect a change on the level of autonomy, competence, relatedness, and ability (T1–T3). These four are measured in self-developed questions and measured on a 6-point Likert scale. Individual scores represent the overall score of individual components, with higher scores indicating higher autonomy, competence, relatedness, and ability.Experiences: the interpretation of the results from the effective measurement and potential implementation strategies for the national implementation of the tool will be explored. One-time interviews will be conducted with 5–10 employees, 5–10 employers, and 5–10 OPs, out of a purposive sample of the RCT participants (after T3). Participants will be selected and invited for voluntary participation in a one-time interview lasting a maximum of 45 min, based on responses from the T3 questionnaire, including factors such as employee satisfaction and perceived utility, aiming for a diverse sample. Topics include (1) the use of the SME tool (employers randomized to the intervention group), (2) the perceived utility of the SME tool (employers randomized to the intervention group and occupational health physicians), (3) perceived support (employees), (4) the implemented implementation strategy for the effectiveness evaluation (all participants), and (5) potential implementation strategies for the national implementation of the SME tool (all participants).

### Statistical analysis

All data will be analyzed according to the intention-to-treat (ITT) principle, as well as the per-protocol (PP) principle [17]. The latter analysis is conducted by tracking the analytics of the website usage through Piwik PRO at least one time if randomized to the intervention group [39]. Due to the nature of the intervention, blinding of participants is not possible. Therefore, the trial is open-labeled. However, data analysis will be performed by a researcher who is blinded to the arms. Primary and secondary outcomes and participants’ characteristics for effect evaluation will be assessed using descriptive statistics. *P*-values ≤ 0.05 will be considered statistically significant. Longitudinal linear mixed models (LMM), including random intercepts and random slopes for each OP, will be used to examine differences between the intervention and control groups for the continuous primary outcome measures as well as all continuous secondary outcome measures: social support from the employer, work performance, quality of working life, self-efficacy, and satisfaction with the resumption of work of the respective employee. Kaplan–Meier survival analysis and Cox regression analysis will be used to compare the time from the first day of sick leave to RTW between the intervention and control groups. In the Kaplan–Meier survival analysis, we will censor patients who dropped out of the study. Covariate adjustment will be performed in the models to account for factors such as gender and age that appear to be prognostic for the outcome measures. We will report reasons for dropout for each randomization group and compare the reasons quantitatively and qualitatively. Dropouts will be included in the analysis by modern imputation methods for missing data. The interviews for the process evaluation will be recorded, transcribed verbatim, and thematically analyzed using MaxQDA [40]. The statistical analyses, including data preparation, will be conducted using SPSS 25.0 and R [28, 41].

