## Sample size calculation

The sample size calculation for this RCT is based on the primary outcome measure: the linear rate of change in the employees’ perceived satisfaction with their employer’s RTW support with respect to the satisfaction at baseline, over a period of 6 months after the beginning of the trial. Based on a prior study involving 3470 employees with various conditions, the expected mean score for the question on satisfaction at baseline is considered to be 2.64 (range 1–5) with a standard deviation of 1.05 [23]. Assuming a 20% improvement after 6 months in the intervention group and no relative improvement in the control group, it is anticipated that the intervention group will achieve a mean score of 3.17 resulting in a linear change rate of 0.53 over a period of 6 months. We estimate the effect of the SME tool on our primary outcome using a linear mixed model with a random intercept and slope for each OP to account for clustering due to OPs recruiting employer–employee dyads. In this model, we estimate the linear effect of the time, and the interaction between time and treatment on the primary outcome using the data collected at 3 and 6 months follow-up. The models are also adjusted for the satisfaction outcome value at the baseline. Assuming an intracluster correlation coefficient of 0.1, both the intervention and control arms need 80 employees to achieve 80% statistical power for detecting a significant difference in the change rate of 0.088 per month of the outcome over time between the intervention and control group at the significance level $$\alpha =0.05$$ [24]. In total, we plan to recruit 202 dyads, which equals 404 participants, to allow for an attrition rate of 20%. The sample size calculation was performed using nQuery [24].

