## Intervention group

After the inclusion of the employee–employer dyad, the SME tool is provided to the employers randomized to the intervention group. The executing researcher (DB) will provide these employers with an e-mail containing their unique website’s URL and details of the study. Employers are asked to use the SME tool during the 6 months follow-up. They will receive an e-mail after 1 and 3 months reminding them to use it, although its usage is not mandated. There are no criteria for discontinuing the allocated intervention.

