## Control group

The URL of the SME tool will remain undisclosed to employers in the control group, ensuring that employers and employees will receive care as usual from their OP. The study will be conducted in the Netherlands. For details regarding the Dutch context and thus the usual care for the control group, we refer to Table 1. During the course of the study, online search engines will not be able to trace the SME tool to prevent possible contamination from the intervention group to the control group. All participants are permitted to receive concomitant care or interventions.

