## Methodological considerations

The SME tool is developed in accordance to the needs and expectations of the SME employers, employees, and OPs. Its relevance and potential impact are further enhanced by its foundation in the Self-Determination Theory and its execution according to the IM approach, building upon previous intervention-developing experiences [15–17]. Additionally, the study incorporates both employers and employees, a methodological approach aligning with previous recommendations [17, 18]. Therefore, the range of outcome measures is on various levels, contributing to a comprehensive understanding of the SME tool’s effect. The additional process evaluation adds to this understanding by providing in-depth insight on how the SME tool is experienced, complementing the quantitative findings. Moreover, the primary outcome measure is focused on the employee. Our choice for the primary outcome measure was guided by the logic model of change (see Additional file 1), expecting that improved RTW support from the employer will lead to higher employee satisfaction and, ultimately, sustainable RTW. However, sustainable RTW is also influenced by many other factors beyond the potential intervention’s impact, for example, the severity of the employee’s condition [42, 43] and sustainable RTW is thus not an outcome of this study.

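### The per-protocol set is chosen by a voluntary behaviour after randomization that only the intervention arm can show, so the per-protocol contrast is not a randomized comparison

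*Protocol article*

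**What the plan says.** The Statistical analysis section of the protocol article names two analysis sets: "All data will be analyzed according to the intention-to-treat (ITT) principle, as well as the per-protocol (PP) principle". The only condition given for the second is "tracking the analytics of the website usage through Piwik PRO at least one time if randomized to the intervention group". No condition is given for control dyads.

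Two other sections settle what that condition means in practice:

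- Intervention group: employers get a personal link and reminder e-mails at 1 and 3 months, "although its usage is not mandated".
- Control group: "The URL of the SME tool will remain undisclosed to employers in the control group", and the site is hidden from search engines during the study.

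The Sample size calculation section says the model for the primary outcome is adjusted for baseline satisfaction. The Statistical analysis section adds adjustment for "factors such as gender and age that appear to be prognostic for the outcome measures". It also says that the analyst will be masked to arm.

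**The concern.** Opening the tool is the employer's own decision, made after allocation, and only intervention employers can make it. Restricting that arm to openers selects on whatever drives the decision. The control arm holds the same mix of would-be openers and would-be non-openers, but they cannot be told apart, so all of them stay in. The two groups compared are then not the groups that randomization formed.

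The likely driver is engagement with the sick-listed employee. The Methodological considerations section links support to the primary outcome, "expecting that improved RTW support from the employer will lead to higher employee satisfaction". If more engaged employers open the tool more often, their employees could become more satisfied without any effect of the tool.

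The label also fits poorly. Since use is not required, an employer who never opens the tool has broken no rule, yet the dyad is left out of the per-protocol set.

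At stake is interpretation. A null ITT result beside a favourable PP result could come from selection alone, and could be taken to mean that the tool works when used.

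**Working it through.** **The plan's own figures**

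- Baseline satisfaction "is considered to be 2.64 (range 1–5) with a standard deviation of 1.05".
- Planned effect: 2.64 × 1.20 = 3.17, a gain of 0.53, "resulting in a linear change rate of 0.53 over a period of 6 months". Per month: 0.53 / 6 = 0.088.
- Standardized: 0.53 / 1.05 = 0.505, or about 0.50 SD.
- Sample size: a two-sample comparison of 0.53 with SD 1.05 (two-sided 0.05, 80% power) needs 62 per arm. With 160 / 40 = 4 dyads per occupational physician and an intracluster correlation of 0.1, the design effect is 1 + 3 × 0.1 = 1.3. Then 62 × 1.3 = 80.6, against the stated 80. Allowing for 20% attrition, 80.6 / 0.8 = 100.75, so 101 per arm and 202 in total, as stated.

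The sample size reproduces to within one dyad per arm. It serves here only as the yardstick for the bias.

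**Bias of the PP contrast when the tool has no effect**

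Let q be the share of employers who would not open the tool. Let d be the would-be user minus would-be non-user difference in the analysed outcome, with means μu and μn.

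- Intervention arm after the PP rule: μu.
- Control arm, unrestricted: (1 − q)μu + qμn.
- Difference: q(μu − μn) = q × d.

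**What d has to be**

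The model adjusts for baseline satisfaction, and the target is a rate of change. A user/non-user gap already present at baseline is therefore removed in part or in full. For a constant gap D, analysis of change from baseline gives zero bias. With baseline as a covariate with coefficient b, the bias is q × D × (1 − b). For example, take q = 0.5, D = 0.5 SD and b from 0.3 to 0.7 (assumed): 0.25 × 0.7 = 0.175 and 0.25 × 0.3 = 0.075, or about 0.08–0.18 SD. So d below means the difference left after baseline adjustment.

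**Range**

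Neither q nor d is in the protocol. Assumed: q = 10–50%, d = 0.1–0.5 SD.

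| q | d (SD) | bias q × d (SD) | bias in points (× 1.05) | share of planned 0.505 SD |
|---|---|---|---|---|
| 0.1 | 0.1 | 0.01 | 0.01 | 2% |
| 0.2 | 0.3 | 0.06 | 0.06 | 12% |
| 0.3 | 0.5 | 0.15 | 0.16 | 30% |
| 0.5 | 0.5 | 0.25 | 0.26 | 50% |

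With d = 0 there is no bias. With d = −0.3 and q = 0.2 it is −0.06 SD, against the tool.

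**Effect on the error rate**

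A rough normal calculation uses 80 controls, 80(1 − q) intervention dyads and SD 1.05, and ignores clustering and the variance removed by baseline adjustment. The nominal 5% becomes 6.5% in the second row, 13.8% in the third and 25.2% in the last. These figures only illustrate the scale.

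**The alternative under the same null**

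The complier-average causal effect (CACE) is, without covariates, the ITT difference divided by (1 − q). If allocation acts only through opening the tool, a null tool gives 0 / (1 − q) = 0 whatever d is.

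Its standard error is about 1 / (1 − q) times that of ITT: 1 / 0.9 = 1.11 at 10% non-use and 1 / 0.5 = 2.0 at 50%. For PP the factor is √[(1/80 + 1/(80(1 − q))) / (2/80)]: 1.03 and 1.22.

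**The case against.** **Size.** The planned model already adjusts for baseline satisfaction, and the baseline item asks about guidance received since the sick leave began, so much of the pre-existing gap should show there. Uptake may also be high: a single visit counts, the employers have consented, and they receive a personal link and two reminders. This stands. It is why d is taken as a residual and why half the planned effect is a corner case, not an expectation.

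**Direction.** A reader might infer that the PP analysis is biased toward the tool. The documents support a loss of comparability. The sign is an inference from the logic model, and it reverses if employers facing harder cases seek out the tool.

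**Ranking.** A reader might also infer that the two analyses share authority because the section does not say which decides. That is a silence. ITT is named before PP, the Design section states a superiority framework, and a condensed article may leave ranking to the full protocol or SAP. The same holds for the timing of the tracking data: nothing shows that the masked analysis will be compromised. Neither silence is counted as an error here.

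**Remedy.** CACE is not a clean correction. It needs allocation to affect satisfaction only through opening the tool. The Methodological considerations section concedes that employees who know their allocation may rate their employer more favourably, and reminder e-mails could prompt support without a visit. Any such direct effect is divided by the uptake share and so enlarged. This stands as a limitation to be stated.

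What the objections leave untouched is the rule itself: it conditions on use in one arm, and no detail left to an SAP can make would-be non-users observable among controls.

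**Conclusion.** The PP contrast as defined is not a randomized comparison and should not be presented as evidence of effect among users. This follows from the stated rule, voluntary use and the undisclosed URL, with no numerical assumption.

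Its size cannot be fixed from the protocol. Under the assumed ranges it runs from about 0.01 to 0.25 SD, or 2–50% of the planned effect. The upper end needs both half of employers never opening the tool and a 0.5 SD gap surviving baseline adjustment. Bias toward the tool is plausible but not certain.

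The ITT analysis is planned, rests on the full randomized arms and is untouched by this selection. A reader might infer that the primary conclusion is at risk; it is not. The point concerns a second analysis that is worth changing because the remedy is cheap.

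**What to change.** 1. Keep ITT as the deciding analysis for this superiority trial, and say so where both sets are named.
2. In place of the PP contrast, estimate the effect of use by a CACE: randomization as instrument for opening the tool at least once, adjusted for baseline satisfaction and the employer characteristics already collected at baseline. Non-use is essentially one-sided because controls have no link. If PP is retained, label it supportive and non-randomized, and state the selection limitation.
3. State the exclusion restriction and the two reasons it may fail: awareness of allocation and the reminder e-mails.
4. Because tracking data exist only in the intervention arm and so reveal allocation, merge them after the masked ITT analysis is locked.

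**Cost.** One secondary analysis changes, with no new data and no change to the sample size. The interval widens relative to ITT by a factor of about 1.1 to 2.0 over the assumed non-use range, against 1.03 to 1.22 for PP, and the estimate rests on an assumption that the trial cannot fully verify.

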### Participants

We aim to include 202 employer–employee dyads, thus a total of 404 participants. Both employees and employers will receive a voucher of 20 euros after participating in the study, i.e., when all questionnaires are completed. Employees at study enrolment should:Be of working age (18–65 years);Have a fixed or temporary employment contract at a SME (≤ 250 employees), with a minimum of 6 months remaining in their contract;Be currently sick-listed or partially sick-listed (≤ 8 weeks), with a risk of long-term absenteeism, based on the likelihood of the duration of sick leave exceeding 2 months as assessed by their occupational physician (OP, in plural OPs);Be able to understand and read Dutch sufficiently, in order to complete the questionnaires;Not have a colleague who is already participating in the study.

Subsequently, the employer of the participating employee will be included. At the time of study entry, the employer should be:An employer, supervisor, (case)manager, or HR manager of a SME (≤ 250 employees). In this study, the employer is appointed by the employee and refers to the person who is in direct contact with the employee, and thus the person who offers the RTW support to the employee;Able to understand and read Dutch sufficiently, in order to use the SME tool and complete the questionnaires.

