#### Recruitment of employers

Subsequently, the OP assesses the eligibility of the employer and will invite eligible employers via telephone or e-mail to participate. A digital informed consent form will be sent to the employer (see Additional file 4). The executing researcher (DB) offers the opportunity for contact and addressing questions. In case the employer is not interested in participation, the employee is unable to participate in the study, as only employer–employee dyads can participate. After signing the form, the dyads will be assigned a unique number in chronological order of inclusion, starting at 001. After inclusion, participants will be asked to complete the baseline questionnaire digitally and the dyads will thereafter be randomized to the intervention or the control group.

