## Participant characteristics and effect measures

### Employees

At T0, the questionnaire contains questions about the personal and work-related characteristics of the employee (e.g., age, gender, reason for sick leave, educational level, work status, type of contract, type of work). Measures for effect evaluation will be assessed as change from baseline at each time point (i.e., T0, T1, T2, and T3), except for one time to event: *total number of sick leave days*. Table 3 depicts an overview of all outcome variables.

**Table 3 Tab3:** An overview of primary, secondary, and process outcome variables

Level	Construct	Measurement instrument; # items	Example item	Response categories	Score calculation
Primary outcome variable					
Employee	Satisfaction with the RTW support from employer	Questionnaire; Self-developed; 1 item	How satisfied are you with the sick leave and return to work guidance you have received from your employer since the sick leave/over the past month/3 months?	1) Very dissatisfied, 2) dissatisfied, 3) neutral, 4) satisfied, and 5) very satisfied	N/A
Secondary outcome variable					
Employee	Social support from employer	Questionnaire; Self-developed; 8 items	How important is it that your employer provides emotional support during sick leave and RTW? (importance); how much emotional support have you perceived form your employer? (amount of support)	1) Very unimportant, 2) unimportant, 3) neutral, 4) important, and 5) very important; 1) Very few, 2) few, 3) neutral, 4) much, and 5) very much	“Importance score” multiplied with “amount of support score” leads to “weighted score”, with higher scores indicating more social support from employer
	Total number of sick leave days	Questionnaire; Self-developed; 8 items	Have you worked in the past month/3 months? This can include both activities in your regular job as well as in adapted work	Yes or no options and open-ended responses to express current employment status, for example date input (e.g., return to work since:../../….)	The average number of working days per week divided by the contracted work days
	Work performance	Questionnaire; Maastricht Instrument for Sustainable Employability (MAISE), subscale 2A ‘work performance’; 6 items	I have the knowledge to perform my job well	1) Completely disagree, 2) disagree, 3) neutral, 4) agree, and 5) completely agree	Mean score, with higher scores indicating better work performance

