Secondary outcomes on the level of the employee include: Social support: social support is assessed through the four facets of support potentially provided by the employer, i.e.: (1) emotional support, (2) practical support, (3) informational support, and (4) appreciative support [23, 31]. The measurement comprises eight questions regarding the importance and amount of support received. The mean score of the importance and amount of support are analyzed separately to take into account the individual difference between the perceived importance. Multiplying all the “importance scores” with each corresponding “amount of support score” leads to a total “weighted score”. A higher score indicates higher social support from the employer, collectively assessing the overall level of social support provided by the employer [32].Total number of sick leave days: the total number of sick leave days involves the assessment of the average number of working days per week over the preceding 4 weeks and the total number of (partial) sick days. This is measured with questions about the current employment status, continuity in the same organization and job position, recent work activities, and details about returning to work if applicable [33]. The total number of sick leave days status is calculated by dividing the average number of working days per week by the contracted work days (T0–T3). Additionally, the total count of (partial) sick days is obtained by measuring the time interval between the initial day of illness and the date of resuming work.Work performance: work performance is measured with subscale 2A from the Maastricht Instrument for Sustainable Employability (MAISE) and refers to the long-term capacity of employees to actively participate in and contribute to the workforce [34]. The six statements, only filled in if work activities have been done in the past 4 weeks, are measured on a 5-point Likert scale. The mean score of the total sum is calculated, with higher scores indicating higher work performance. These scales have demonstrated reliability and validity across diverse employee populations [34].Quality of working life: quality of working life is measured with subscale 2 from the Quality of Working Life Questionnaire for cancer survivors (QWLQ-CS). This validated questionnaire comprises items designed to capture dimensions of work-related perceptions and is measured on a 6-point Likert scale. Only subscale 2 about “understanding and recognition in the organization” consisting of five items is included, as we only anticipate change in this subscale according to our logic model of change (Additional file 1). The sum represents the overall score, with a higher score corresponding to a higher feeling of understanding and recognition in the organization. The questionnaire’s internal consistency, construct validity, and group-level reproducibility have been established, rendering it suitable as a patient-reported outcome measure for interventions [35, 36]. The questionnaire has also been applied beyond cancer-related contexts, such as in cases of chronic inflammatory bowel disease [37].

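### Time to RTW is counted from the first sick day, before randomization and without stated delayed entry, and the article leaves open whether partial or adapted work already counts as RTW

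*Protocol article*

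**What the plan says.** All places are in the protocol article.

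- **Clock and method.** Statistical analysis: Kaplan-Meier and Cox regression are used to "compare the time from the first day of sick leave to RTW between the intervention and control groups". Dropouts are censored. Nothing is said about when a participant enters the risk set.
- **Who enters.** Participants: an employee must "Be currently sick-listed or partially sick-listed", for no more than 8 weeks, and must be at risk of long absence, "based on the likelihood of the duration of sick leave exceeding 2 months as assessed by their occupational physician".
- **When randomization happens.** Recruitment of employers: "participants will be asked to complete the baseline questionnaire digitally and the dyads will thereafter be randomized". The Randomization section likewise releases the allocation only after all baseline measurements.
- **The event.** Employees, total number of sick leave days: "the total count of (partial) sick days is obtained by measuring the time interval" that ends on the date of resuming work. Whether this means full or partial resumption is not stated.
- **What the questionnaire counts as work.** Table 3, example item for the same outcome: "This can include both activities in your regular job as well as in adapted work".

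**The concern.** There are two separate problems, and they act differently.

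**Clock.** The time origin lies up to about 8 weeks before enrolment, plus the time needed for employer consent and the baseline questionnaires. Anyone who fully returned in that window could not be enrolled, so each participant brings a stretch in which full RTW was impossible by selection. If everyone is treated as at risk from day 0, early survival is overstated. A reader who takes the curve or median as the usual length of sick leave would be misled.

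**Event.** If any work or adapted work is RTW, a partially sick-listed employee who is already working at enrolment has had the event before the employer receives the tool. The intervention cannot influence such an event. It adds noise to the comparison and weakens a real effect.

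The first problem concerns the description of absence. The second can reach the treatment comparison.

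**Working it through.** **No figure to reproduce.** The article gives no RTW rate, entry-time distribution or share partially sick-listed. Its sample size rests on the satisfaction score and plays no part here. All rates below are assumptions.

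**1. Clock, closed form.** Assume potential entry is uniform over days 0 to 56 and RTW is exponential with rate l = ln 2 / median. Enrolment requires T > entry, which has probability c = (1 − exp(−56l)) / (56l). After day 56 the uncorrected curve is S(t) = exp(−lt)/c, so its median is the true median + ln(1/c)/l.

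| True median (days) | c | Uncorrected median | Excess | Absent at day 56: true | Uncorrected |
|---|---|---|---|---|---|
| 90 | 0.812 | 117.0 | 27.0 | 0.65 | 0.80 |
| 120 | 0.854 | 147.2 | 27.2 | 0.72 | 0.85 |
| 180 | 0.900 | 207.5 | 27.5 | 0.81 | 0.90 |

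**2. Clock, simulation.** 20,000 subjects per scenario, with entry of those enrolled uniform over weeks 1 to 8, exponential return and 26 weeks of follow-up from entry.

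| True median (weeks) | Uncorrected | Delayed entry | Difference |
|---|---|---|---|
| 8 | 12.8 | 9.2 | 3.6 |
| 12 | 16.5 | 12.7 | 3.7 |
| 16 | 20.5 | 16.9 | 3.6 |
| 26 | 30.6 | 27.2 | 3.4 |

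Delayed entry lies about one week above the true median because nobody is under observation in week 1: it estimates duration among those absent at week 1, whose median is 1 + the true median. A hand check for 16 weeks: l = 0.0433; mean of exp(l × entry) = (exp(8l) − exp(l))/(7l) = 1.220; uncorrected median = 16 + ln(1.220)/l = 20.6; and 20.6 − 17 = 3.6.

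If nobody returns before week 8, both methods give the same median (19.9 weeks in one scenario, 24.2 in another).

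**3. Clock, arm comparison.** With a true hazard ratio of 1.5 after randomization and no events before it, Cox regression from the first sick day gives 1.49.

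**4. Event.** The two descriptions of the outcome point in different directions:

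- The Table 3 item counts adapted work as having worked, which suggests that any resumption ends the interval.
- The Employees section counts partial sick days inside the interval, which suggests that partial work does not end it.

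Under the any-work reading, with a true median of 16 weeks and a true hazard ratio of 1.5:

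| Assumed share already working | Hazard ratio | Control median (weeks) |
|---|---|---|
| 0% | 1.49 | 20.7 |
| 10% | 1.39 | 17.7 |
| 20% | 1.35 | 15.6 |
| 40% | 1.27 | 9.1 |

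Leaving those employees out and using delayed entry gives 1.50, 1.48, 1.48 and 1.53. That spread around 1.5 shows the simulation noise, about 0.03. With no true effect, 160 employees and a 20% share, the type I error is 0.047 (1,000 replicates).

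**The case against.** **Origin and SAP.** The first sick day is a natural origin: the phases in the tool and the employer's two-year duty run from it. It is valid with delayed entry, which an analysis plan could specify. This stands in part. Silence on delayed entry in an article is not itself an error. But the article does fix the origin, and that origin is safe only with such a rule.

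**What the curve estimates.** After week 8 the uncorrected curve correctly describes total absence among those enrolled, and the article promises a comparison of arms, not a population median. This stands. The curve is too long only when read as the duration of sick leave in general.

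**The physician's forecast.** Selecting employees expected to be absent for more than 2 months limits early returns, and entry on day 0 is implausible given the recruitment steps. This also stands: the excess shrinks, and it vanishes if nobody returns before week 8. But a forecast is not a guarantee.

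**Stronger readings a reader might infer.** Three go beyond the documents:

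- *Every partially sick-listed employee has already had the event.* No such rule is stated. Table 3 shows one example item of eight, and counting partial sick days up to resumption points to full return.
- *The arm comparison is invalid.* The clock leaves the hazard ratio essentially intact, and the type I error stays near 5% even with events before randomization.
- *Medians are too long overall.* The clock lengthens them and events before randomization shorten them. The net direction is unknown, and the two cannot be relied on to cancel.

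**Conclusion.** The point holds in two limited parts, both for a secondary outcome.

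1. The clock starts before randomization among people selected for still being absent. Without delayed entry, the median read as sick-leave duration is too long by about 3.5 to 4 weeks under uniform entry and exponential return, and by as little as zero if no one returns before week 8. The between-arm hazard ratio is barely affected.
2. RTW is not fixed as one event, and Table 3 and the Employees section must be reconciled. Only if any work counts are there events before randomization. The effect would then be loss of sensitivity rather than false positives, with 1.5 falling to between 1.39 and 1.27 for assumed shares of 10 to 40%.

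The direction of each effect follows from the design. The sizes rest on assumed rates and shares that the article does not give. The correction is worth making because it is cheap, but it does not touch the primary analysis.

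**What to change.** - **Clock.** Start at randomization, with prior sick-leave duration as a covariate. Alternatively, keep the first sick day as origin and let each employee enter the risk set at randomization.
- **Event.** Reconcile Table 3 with the Employees section into one RTW definition that cannot have been met at randomization, for example full return to contracted hours. The clock change alone is not enough: under the any-work reading, employees already working would have an event time before their entry time and would drop out of the analysis.
- **Baseline status.** Adjust for partial or full sick-listing at baseline, and state how work resumed before randomization is handled.

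The cost is a change of analysis wording, best made before results are seen. The sick-leave and return dates are already collected and the randomization date is known. The drawback is fewer events within 6 months if full return is chosen.
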